For monitoring and assessing intervention adherence, the following methods will be employed: (1) Subjective assessment methods: The 3-day 24-h dietary recall and Food Frequency Questionnaire (FFQ) will be used to record egg consumption timing, quantity, and accompanying foods, with cross-validation between the two methods. Trained interviewers will conduct telephone follow-ups weekly using open-ended questions such as: “What did you eat for your three meals yesterday? Did you consume an egg? At what time?” (2) Objective assessment methods: Fasting venous blood samples will be collected to measure biomarkers of omega-3 fatty acid intake, specifically the Omega-3 Index (the percentage of EPA and DHA in total fatty acids in red blood cell membranes). (3) Process monitoring: Empty egg packaging from the previous week will be collected, and remaining egg counts will be verified against self-reported consumption.

Through this three-tier adherence management system (supply guarantee, reminder supervision, and biological verification), we will maximize the assurance, supervision, and monitoring of stable egg consumption behavior among elderly participants during the 12-week intervention period, thereby enhancing the internal validity of the study.

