**Figure 1 F1:**
[figure not shown]
The study flowchart.

**Table 2 T2:** Time schedule for enrollment, intervention, follow-up, and assessment.

Time point	Enrollment and informed consent	Questionnaire survey	Biological samples collection (blood, urine, stool samples)	Egg consumption and medication/supplement use	Clinical measurements	Outcome evaluation
Enrollment period	√	√		√		
(Baseline week)				√		
The first day of enrollment			√	√		
Intervention phase I (Week 1–4)				√		
First follow-up (end of Week 4)		√	√	√		
Intervention phase II (Week 5–8)				√		
Second follow-up (end of Week 8)		√	√	√		
Intervention phase III (Week 9–12)				√		
Third follow-up (end of Week 12)		√	√			
Laboratory testing phase					√	
Outcome analysis phase						√

**Table 3 T3:** Details of the intervention components and responsible personnel.

Intervention components	Responsible personnel
Group A: omega-3 PUFA-enriched eggs group	
**Dietary intervention (egg consumption):** Tuesday to Saturday: One **boiled omega-3 PUFA-enriched egg daily**; Monday and Sunday: **Egg-free days** (no egg or egg product consumption); Duration: 12 weeks. **Quality control:** Eggs will be distributed weekly, with daily intake recorded. “Verbal + written” reminders will be provided on egg-free days; the diary will be verified and marked for “additional egg/egg product consumption.”	Participants (eggs consumption and diary-keeping) On-site study staff (Distribution of eggs and diaries; compliance monitoring and review)
**Adherence management:** The “Participant Diary” will be collected and reviewed daily. On the first day of each week, the next week's eggs will be distributed, and the previous week's diaries will be collected and reviewed. **Quality Control:** Missing entries will be completed on the same day; anomalies (under-consumption, over-consumption, or non-adherence to egg intake requirements) will be recorded and marked immediately. Compliance will be calculated as “actual consumption/required consumption.”	On-site study staff (Weekly distribution of eggs and collection of diaries) Remote study staff (Daily diary review and quality control)

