**Usual diet:** Participants will maintain their habitual dietary patterns throughout the 12-week study period. **Quality control:** Potential contamination behaviors, including self-initiated consumption of eggs or egg products will be monitored through diaries and dietary surveys. These data will be used as covariates or for sensitivity analyses.	Participants (record-keeping)
**Follow-up assessments (Weeks 4, 8, and 12):** Follow-up visits and sample collection will be conducted at the same frequency as Groups A and B, including questionnaire administration, physical measurements, and blood, urine, and stool sample collection. All samples will be transported via cold chain. **Quality control:** Quality control procedures will be identical to those in Groups A and B, including on-site questionnaire review, threshold-based review of physical measurements, and end-to-end sample traceability.	On-site study staff (Distribution of eggs and diaries; compliance monitoring and review)
**Data management (all groups):** Data recording, review, and database lock. **Quality control:** Double data entry and review; source data verification for outlier detection.	Statistician

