## Data entry and analysis

7

**Data entry:** Questionnaire data will be collected directly via electronic forms with built-in logic checks to ensure the accuracy and completeness of data entry, minimizing errors in data recording.

**Statistical analysis:** Statistical analyses will be performed using SPSS 24.0 and R 4.2.0 software. For baseline variables, continuous variables will be analyzed using one-way analysis of variance (ANOVA) or kruskal-wallis tests, while categorical variables will be analyzed using chi-square tests or Fisher's exact tests.

For longitudinal outcome measures, mixed-model repeated measures analysis of variance (MMRM) with an unstructured covariance matrix will be adopted as the primary analytical method. This model will include intervention group, time point, and group × time interaction as fixed effects, with subject-specific random intercepts. Pre-specified covariates (including age, sex, body mass index (BMI), baseline dietary intake, physical activity, baseline clinical parameters, and compliance) will be adjusted in the primary analysis based on their correlation with outcomes and clinical relevance.

Missing data will be handled using intention-to-treat (ITT) analysis with mixed models, which can accommodate unbalanced data under the missing at random (MAR) assumption. Sensitivity analyses will include complete case analysis and multiple imputation by chained equations (MICE) to verify the robustness of the results.

For multi-omics analyses (microbiome and metabolomics), Benjamini-hochberg false discovery rate (FDR) correction (*q* < 0.05) will be applied to control the expected proportion of false positives among the results. Microbiome data will undergo centered log-ratio (CLR) transformation to address compositional data constraints. Non-parametric methods [Friedman test, permutation-based multivariate analysis of variance (MANOVA)] will be used when the assumptions of normality or homogeneity of variance are violated. Principal coordinate analysis (PCoA) based on bray-curtis distances will be used to analyze microbiome composition, and principal component analysis (PCA) will be applied to metabolomics data. Associations between the microbiome and metabolome will be analyzed using sparse partial least squares (sPLS) or canonical correlation analysis (CCA), with FDR correction applied to ensure the reliability of the results.

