
Several other limitations should be acknowledged. First, complete participant blinding will not be achievable due to the absence of egg distribution in the blank control group, which may introduce expectation or behavioral bias. Second, dietary intake and compliance will be partly self-reported, potentially leading to recall or social desirability bias. Such bias will be minimized through strict quality control, double data entry, and validation using objective indicators. Third, the 12-week intervention period in this study will be sufficient to evaluate the acute effects of omega-3 PUFA-enriched eggs on blood lipids, gut microbiota, and metabolomic profiles; however, considering the ecological resilience of gut microbiota, longer intervention durations or post-intervention follow-up will be beneficial for assessing the sustainability of these changes. Future research will explore 6-month intervention designs with washout periods to verify the stability of gut microbiota alterations. Finally, variability in cooking methods and dietary substitution may influence individual exposure levels and metabolic outcomes. Although boiled eggs will be provided to participants living near community hospitals, cooking practices cannot be fully controlled in elderly individuals with limited mobility. Therefore, dietary surveys and follow-up records will be incorporated for covariate adjustment and sensitivity analyses, enhancing the robustness of result interpretation.

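### The primary intention-to-treat model adjusts for compliance, a post-randomisation ratio with no value in the blank control arm, and leaves its covariate list open

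*Protocol article*

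**What the plan says.** Section 7 (Data entry and analysis) sets a repeated-measures mixed model as the primary method: "This model will include intervention group, time point, and group × time interaction as fixed effects, with subject-specific random intercepts". It then gives the covariates: "Pre-specified covariates (including age, sex, body mass index (BMI), baseline dietary intake, physical activity", continuing to "baseline clinical parameters, and compliance) will be adjusted in the primary analysis based on their correlation with outcomes and clinical relevance". The next paragraph of the section describes the analysis as intention-to-treat: "Missing data will be handled using intention-to-treat (ITT) analysis with mixed models".

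Table 3 (Group A, adherence management; Group B follows the same procedures) defines compliance as "actual consumption/required consumption", taken from on-trial diaries. Under Section 3.2 and Table 3 the blank control group keeps its usual diet. Its egg intake is recorded only as possible contamination, and of those records Table 3 says: "These data will be used as covariates or for sensitivity analyses". The Discussion adds that "dietary surveys and follow-up records will be incorporated for covariate adjustment and sensitivity analyses".

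Section 5.3 makes the group × time interaction for fasting triglycerides (TG) at Weeks 0, 4, 8 and 12 the primary test. The primary comparison is enriched versus regular eggs, and other pairs are exploratory. Table 4 schedules physical activity at all four visits.

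**The concern.** An intention-to-treat estimate compares arms as randomised. Compliance builds up after randomisation and may respond to the arm. If it does, conditioning on it can remove part of the effect that works through intake. It can also make the arms differ on whatever drives both compliance and TG, such as general health behaviour.

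The blank control arm raises a separate problem. With no eggs required, the ratio does not exist there, so the model as described cannot use all three arms without an unstated coding rule.

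Two wording faults sit in the same sentence. Physical activity is not marked as baseline, although diet and clinical parameters are. The list is called pre-specified, yet adjustment is tied to correlation with outcomes, which a reader could take as permission to settle the list once data are in. At stake is whether the main result rests on the randomised contrast and on a model fixed beforehand.

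**Working it through.** **1. The plan's own figure.** Section 2.3 gives SD 58 mg/dL, difference 35 mg/dL, two-sided 5%, 80% power and 25% dropout. With σ² in the numerator, n = 2(1.96 + 0.84)² × 58² / 35² = 15.68 × 3364 / 1225 = 43.06, so 44 per group. Then 44 / 0.75 = 58.7, so 59, set at 60. This reproduces the plan. No covariate enters it, so removing compliance leaves 44, 59 and 60 as they are. Power with 60 × 0.75 = 45 evaluable per arm is about 0.82.

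**2. Blank control arm.**
- Compliance missing: all 60 participants of that arm leave the model.
- Compliance coded 0, at a single visit, with 60 per arm and SD 58. Assume compliance is uniform on 0.7–1.0 in the egg arms (mean 0.85, variance 0.3²/12 = 0.0075).
  - SE of enriched versus blank without compliance: 58 × √(2/60) = 10.6 mg/dL.
  - SE of the compliance slope: 58 / √(120 × 0.0075) = 61.1.
  - SE of the contrast with compliance: √(10.6² + (0.85 × 61.1)²) ≈ 53 mg/dL. One simulated sample gave 54.8.

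**3. When the group × time contrast moves.** With complete data and Week 0 TG in the response, the adjusted mean for arm g at visit t is ȳ(g,t) − β(t) × C̄(g), where C̄(g) is mean compliance. The change-from-Week-0 difference between arms A and B therefore shifts by −[β(t) − β(0)] × [C̄(A) − C̄(B)]. The shift is zero if mean compliance is equal, or if β is constant over time. One simulated data set (60 per arm, compliance generated with an arm difference, complete data) shows this:

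| Form of compliance in the model | Week 4 | Week 8 | Week 12 |
|---|---|---|---|
| Not included | 28.32 | 32.53 | 19.95 |
| Time-constant main effect | 28.32 | 32.53 | 19.95 |
| Compliance × time | 26.21 | 18.88 | 11.60 |
| Post-baseline term only | 16.40 | 20.61 | 8.03 |

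Only the differences between rows matter. The last row is lower than the first by 11.92 at every visit, as the formula implies. The protocol does not say which form is meant. With dropout, the exact equality of the first two rows is no longer guaranteed.

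**4. Size of the bias for enriched versus regular eggs.** Assumptions: no true effect; compliance (SD 1) and TG share a cause U; U loads 0.7 on compliance and correlates g = 0.3 to 0.5 with TG in absolute value, better behaviour going with lower TG; mean compliance differs by d SD between arms. The shift is 0.7 × g × 58 × d, which is 12.18d for g = 0.3 and 20.3d for g = 0.5. The rejection rates come from a follow-up comparison with 45 per arm and 4,000 runs.

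| Arm difference d (absolute) | Shift, mg/dL | Rejection at nominal 5% |
|---|---|---|
| 0 | 0 | about 5% |
| 0.25 SD | 3.0–5.1 | 5.6–7.4% |
| 0.5 SD | 6.1–10.2 | 7.8–14.0% |
| 1.0 SD | 12.2–20.3 | 14.9–33.9% |

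Without compliance in the model, the estimate stayed near 0 and rejection near 5% throughout. Under these assumptions, lower compliance in the enriched arm produces a spurious benefit and higher compliance a spurious harm.

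**5. Could compliance differ between blinded arms?** Section 3.3 provides for feedback to participants on biomarker changes, with the Omega-3 Index as the example, in order to raise motivation. The enriched eggs are meant to change omega-3 markers more than regular eggs do, so the feedback could differ by arm. That is a possible route, not evidence of a difference.

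**The case against.** The strongest reply is that the primary comparison is well protected. Both egg arms follow the same schedule, and Section 4.3 blinds participants and staff to egg type. If compliance has the same distribution in the two arms, adjusting for it does no harm. A time-constant main effect with Week 0 TG in the response and complete data leaves the primary contrasts untouched. The missing denominator concerns an arm whose comparisons are exploratory. All of this stands, and it limits the point to a risk of bias in the primary comparison. It does not justify keeping the covariate: the protocol does not fix the form, it plans for 25% dropout, and the feedback in Section 3.3 weakens the assumption of equal compliance.

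Three stronger readings are tempting but not supported:
- A reader might infer that the Omega-3 Index is the compliance covariate, so that adjustment would remove the effect under test. Section 3.3 lists it as an objective adherence measure ("specifically the Omega-3 Index (the percentage of EPA and DHA in total fatty acids in red blood cell membranes"), but the only formula for compliance is the egg ratio, and nothing places the Index in the TG model.
- A reader might infer that on-trial diet and egg records enter the primary model. Table 3 and the Discussion mention covariate use without naming that model, and Section 7 lists baseline dietary intake.
- A reader might infer that outcome-driven selection invalidates the 5% error rate. The sentence also calls the covariates pre-specified and cites clinical relevance. Choosing baseline covariates by their correlation with outcome, without regard to arm, does not of itself bias the comparison. The fault is that the list is left open.

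**Conclusion.** The point holds in limited form. As written, the primary intention-to-treat model contains a post-randomisation covariate that has no value in one of its three arms. The damage to the blank-control contrasts follows from the definition: the arm is lost if the value is missing, or, if it is coded 0 and compared at a single visit, the SE rises from about 10.6 to about 53–55 mg/dL under the assumed spread of compliance.

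The protocol does not show that the enriched-versus-regular comparison is biased; it can be. Bias needs unequal compliance between the egg arms and a form of adjustment that alters group × time. Under the stated assumptions it would be about 3–5, 6–10 or 12–20 mg/dL for differences of 0.25, 0.5 or 1.0 SD, which at the upper end is more than half of the 35 mg/dL design difference. These are illustrations with assumed inputs, not predictions. The unlabelled physical activity term and the selection wording are lesser faults of the same sentence. Because the primary analysis is affected and the repair is free, it should be corrected before recruitment starts.

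**What to change.** In Section 7:
- Delete compliance from the covariates of the primary model.
- Fix the list now, as baseline values only: age, sex, baseline BMI, baseline diet, baseline physical activity and named baseline clinical parameters.
- Delete the clause that ties adjustment to correlation with outcomes.
- Use baseline TG once, either as the Week 0 response or as a covariate. Section 5.3 already includes Week 0 in the outcome trajectory.

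In Section 7, Table 3 and the Discussion, confine compliance and on-trial diet or egg records to analyses labelled supplementary, with compliance analysed in the two egg arms only.

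The cost is a change of wording. No further data or participants are needed, the sample size stays at 44, 59 and 60 per group, and Table 1 gives the trial as not yet recruiting.

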### Sample size calculation

2.3

This three-arm randomized controlled trial will adopt an allocation ratio of 1:1:1. The primary outcome will be the change in fasting serum triglyceride (TG) levels from baseline to the end of the intervention. The main effect to be tested will be the difference in TG level changes between the omega-3 PUFA-enriched eggs intervention group and the regular eggs group. Based on previous dietary intervention studies in populations with metabolic syndrome, the estimated standard deviation of fasting serum TG is approximately 58 mg/dL (baseline TG level: 140.9 ± 58.0 mg/dL) (19). Sample size estimation will be based on data from a prior randomized trial, which reported a 35 mg/dL difference in triglyceride (TG) levels between participants consuming omega-3 PUFA-enriched eggs (152.476 mg/dL) and those consuming regular eggs (187.333 mg/dL) (20). Accordingly, the minimal clinically meaningful difference (δ) will be set at 35 mg/dL. Assuming a two-sided significance level of 0.05 and 80% statistical power (1–β = 0.80), the required sample size will be computed using the standard formula for comparing means between independent groups:

$$\begin{array}{l} N=\frac{2{\left(Z_{1-\frac{\alpha }{2}}+Z_{1-\beta }\right)}^{2}}{\delta^{2}} \end{array}$$

Where Z_1−α/2_ = 1.96, Z_1−β_ = 0.84, σ = 58 mg/dL, and δ = 35 mg/dL. Consequently, to meet the statistical power requirements for the primary comparison, approximately 44 participants per group will be needed. Considering a potential dropout rate of approximately 25% in 12-week dietary intervention studies among elderly populations (21), the sample size will increase accordingly:

$$\begin{array}{l} n=\frac{44}{1-0.25}\approx 59 \end{array}$$

Therefore, the final target sample size will be set at 60 participants per group, yielding a total of 180 participants across the three arms.

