### Primary outcome

5.3

The primary outcome will be defined as the longitudinal trajectory of fasting triglycerides (TG) measured at Weeks 0, 4, 8, and 12. The primary statistical analysis will focus on the group × time interaction, indicating differences in TG trends over time among intervention groups. The pre-specified primary comparison will be between the omega-3 PUFA-enriched egg group and the standard egg group to evaluate intervention efficacy. Exploratory pairwise comparisons will also be conducted for other group combinations not specified in the primary hypothesis.

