For bias control, randomization sequences will be generated by independent statisticians, and allocation concealment will be ensured using opaque envelopes. Group assignment will be performed by non-enrolling investigators to minimize investigator bias. Regarding blinding, this trial will adopt an “open-label control with blinded intervention arms” design. The two types of eggs (omega-3 enriched vs. regular) will be identical in appearance and differentiated only by coded labels. Although participant blinding will not be feasible in the blank control group, the limitations of blinding will manifest in the following aspects. First, the open-label status of the blank control group will make participants explicitly aware that they are receiving no intervention, potentially inducing negative expectation effects and feelings of deprivation, which may lead to deterioration in health behaviors or reporting bias in symptom assessment. Although participants in the two blinded egg groups will be unaware of the specific egg type they receive, being informed of “receiving an egg intervention” may still generate positive expectations. The gradient distribution of expectation intensity across the three groups (hypothesized as: blank control < regular eggs < omega-3 PUFA-enriched eggs) will create an imbalance in expectation effects, making it impossible to distinguish whether between-group differences originate from the intervention itself or from differential psychological expectations. Second, participants in the control groups may voluntarily modify their dietary behaviors (e.g., increasing egg consumption) to compensate for the sense of deprivation, resulting in inter-group contamination and dilution of intervention effects. Third, despite the blinding of intervention administrators, outcome assessors, and data analysts, subjective outcome measures will remain susceptible to participant expectations; while objective biochemical indicators, although relatively robust, could still be confounded by behavioral changes in the control groups. Furthermore, divergent expectation levels among the three groups may lead to heterogeneous variance in outcome variables, and the potentially higher attrition rate in the blank control group could cause non-random missing data, threatening the validity of statistical inference. These limitations will exert multidimensional impacts on internal validity. First, expectation effects cannot be excluded as a confounding factor, meaning that the observed effects of omega-3 PUFA-enriched eggs may represent a combination of true biological effects, placebo effects, and negative expectation effects from the control group, with the weighting of each component remaining indeterminate. Second, it will limit the generalizability of the results to scenarios with uniform blinding or open-label conditions. In conclusion, the open-label status of the control group will constitute a source of systematic bias. Causal language should be used cautiously when interpreting results; priority should be given to objective biochemical indicators, and sensitivity analyses alongside process evaluations will be conducted to quantify the extent of bias. Nevertheless, allocation concealment, third-party randomization, assessor blinding, and post-data-lock unblinding will also be implemented to partially attenuate these biases.

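### The named missing-data sensitivity analyses cannot test the non-random dropout that the Discussion warns of in the blank control arm

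*Protocol article*

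**What the plan says.** Section 7 (Data entry and analysis) handles missing outcomes through the mixed model, "which can accommodate unbalanced data under the missing at random (MAR) assumption". It then names two checks and gives their purpose: "Sensitivity analyses will include complete case analysis and multiple imputation by chained equations (MICE) to verify the robustness of the results".

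Section 8 (Discussion), on the limits of blinding, raises a different possibility: "the potentially higher attrition rate in the blank control group could cause non-random missing data, threatening the validity of statistical inference". The same paragraph later promises that "sensitivity analyses alongside process evaluations will be conducted to quantify the extent of bias", without naming a method. The other sensitivity analyses mentioned (Table 3 for the blank control group, and the limitations in Section 8) concern extra egg consumption, cooking practice and diet, not missing data.

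Two further statements fix the reach of the point. Section 5.3 says: "The pre-specified primary comparison will be between the omega-3 PUFA-enriched egg group and the standard egg group to evaluate intervention efficacy". It continues: "Exploratory pairwise comparisons will also be conducted for other group combinations not specified in the primary hypothesis". Section 2.3 sets the expected amount of missing data: "Considering a potential dropout rate of approximately 25% in 12-week dietary intervention studies among elderly populations".

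**The concern.** A sensitivity analysis for missing data is useful when it relaxes the assumption that is in doubt. Here the doubtful assumption is MAR, and the document itself raises the doubt. Neither named check relaxes it. Standard MICE imputes from the same conditional distributions that the mixed model uses implicitly. Complete-case analysis discards the partial records and so leans on a stronger condition.

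What is at stake is the meaning of a later sentence in the results paper. If the mixed model and MICE agree, the plan's wording invites the statement that the findings are robust to missing data. That agreement is expected whether or not dropout depends on unobserved triglycerides, so it carries no information on the question. If the complete-case result differs, the reader cannot tell why, because it can differ under MAR as well. The contrasts with the blank arm are the most exposed, since that is where the Discussion expects attrition to be heavier.

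**Working it through.** **Inputs from the documents.** SD 58 mg/dL, δ = 35 mg/dL, two-sided α = 0.05, power 80%, dropout 25% (all Section 2.3); visits at Weeks 0, 4, 8 and 12 (Section 5.1).

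**The plan's own figure.** n = 2(1.96 + 0.84)² × 58² / 35² = 2 × 7.84 × 3364 / 1225 = 43.06, so 44 per group. Then 44 / (1 − 0.25) = 58.7, so 59, set at 60. This reproduces. At 25% dropout, 60 × 0.25 = 15 participants per arm would lack a Week 12 value.

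**Assumption behind each method.**
- Mixed model: MAR given the variables in the model and the observed outcomes.
- Standard MICE: MAR given the variables in the imputation models.
- Complete case: missingness completely at random, or dependent only on covariates in the model. For a repeated outcome this is generally stricter than MAR.

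None of the three allows missingness to depend on the unseen value.

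**Size of a departure.** Let p be the fraction missing in an arm and s the amount by which the true mean of the missing values exceeds the MAR prediction. The arm mean moves by p × s, and a contrast moves by p₁s₁ − p₂s₂. The shifts s, and the 35% dropout, are assumptions; 25% is the plan's figure. With the shift in one arm only:

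| s (mg/dL) | p = 0.25 | p = 0.35 |
|---|---|---|
| 10 | 2.5 | 3.5 |
| 20 | 5.0 | 7.0 |
| 35 | 8.75 | 12.25 |

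Against δ = 35, the 25% column is 2.5/35 = 7%, 5.0/35 = 14% and 8.75/35 = 25%. If p and s are the same in both arms, the contrast moves by zero.

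**Do the named checks reveal it?** A simulation used four visits, SD 58, a true difference of 0, monotone dropout and 200,000 per arm. Two inputs are assumed: within-person correlation 0.7, and a dropout log-odds slope of 1.5 per SD of triglycerides where dropout depends on the outcome. The mixed model was represented by maximum likelihood under multivariate normality. Entries are the estimated difference in change to Week 12 (mg/dL), first arm minus second, so any value away from 0 is bias apart from simulation error.

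| Dropout in first arm / second arm | Mixed model | MI | Complete case |
|---|---|---|---|
| Random 25% / MAR 25% | 0.21 | 0.25 | −1.40 |
| Random 25% / MNAR 25% | 5.66 | 5.63 | 2.31 |
| Random 25% / MNAR 35% | 7.75 | 7.68 | 2.77 |
| MNAR 25% / MNAR 25% | 0.03 | 0.01 | 0.13 |
| MNAR 25% / MNAR 35% | 2.20 | 2.13 | 0.68 |

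The mixed model and MI agree closely in every row, whether right or wrong. Complete case departs from them under MNAR, but also under MAR. In the second row the shift needed to correct the MNAR arm is 21.55 mg/dL, and 0.25 × 21.55 = 5.4, close to the 5.66 found, so the p × s rule describes the bias adequately.

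**The case against.** The best case for the plan has four parts.

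**The list is open.** Section 7 says what the sensitivity analyses will include, and Section 8 promises further unspecified ones. A fuller analysis plan could contain an MNAR analysis, so a reader should not infer that none will be done. This stands. What remains is that the article chose two analyses, stated that their purpose is to verify robustness, and chose methods that cannot do so for the threat it names.

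**The primary comparison is not what the Discussion is worried about.** The warning concerns the blank arm, whose contrasts are exploratory. Participants in both egg arms are blinded to egg type, and bias cancels between them if mechanism and rate are equal. This largely stands. The Discussion does hypothesise different expectation levels even between the two egg arms, but it does not link that difference to dropout.

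**The wording is conditional.** The text says that attrition may be higher and could lead to non-random missingness; it does not predict it. Unequal attrition alone is compatible with MAR given arm, and the phrase used might loosely mean no more than not completely random. The first part stands. The loose reading is possible, but the Discussion presents the problem as a threat to valid inference, which a model valid under MAR would already meet.

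**The three analyses need not all agree.** A reader might infer that non-random dropout would leave no trace in the planned results. The simulation does not support that: complete case was biased by 2.31 where the other two were biased by about 5.6. The trace is simply uninterpretable.

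**Conclusion.** The point holds in limited form. The document raises possible non-random missingness, and the only missing-data sensitivity analyses it names assume MAR or something generally stricter. Agreement between the mixed model and MICE cannot be offered as evidence against that threat.

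The effect on a blank-arm contrast is dropout fraction × shift: 2.5 to 8.75 mg/dL at 25% dropout for assumed shifts of 10 to 35 mg/dL in one arm. No document figure fixes the shift, and the simulated biases depend on the assumed correlation and dropout slope, so both are illustrations and not forecasts.

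A reader might go further and infer that the primary effect is overstated by a set amount. For example, if enriched-arm dropouts lost all benefit, an estimate of 35 mg/dL would become 35 × 0.75 = 26.25 mg/dL. The documents do not support using that as the measure of this problem. They describe no such mechanism in the enriched arm, and the calculation also changes the question, from the effect had everyone continued to the effect including loss of benefit after dropout. For the primary comparison the concern is conditional on non-random missingness that differs between the two egg arms.

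**What to change.** Keep the MMRM as the primary analysis. In Section 7, add one MNAR sensitivity analysis built on the MICE already planned: delta-adjusted imputation, with the triglyceride shift varied separately by arm and the tipping point reported. Apply it to the contrasts with the blank arm and, as a check, to the enriched-versus-regular contrast. Fix the range of shifts before unblinding, since shifts chosen afterwards carry little weight; 10, 20 and 35 mg/dL would serve as an example range, the last being the plan's own δ. State in the text that agreement of MMRM, MICE and complete-case results will not be described as evidence against non-random missingness.

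The cost is a few sentences and a little extra programming, with no new data or participants. Reported robustness may look slightly less favourable.
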